### Interventions

A basic antiemetic plan (dexamethasone, ramosetron, or tropisetron) will be used in the control group. The remaining three groups will be given antiemetics and receive electroacupuncture at the ST36, CV12, and ST36-CV12 points. If vomiting cannot be controlled, a doctor will prescribe medication to relieve the symptoms according to the disease type.

### Control group

The control group will receive only a basic antiemetic regimen. This protocol will be delivered according to the American Society of Clinical Oncology clinical practice guidelines [12]. We chose 5-HT_3_ antagonists (ramosetron or tropisetron, beginning on day 1 of chemotherapy and taken continuously for 3–5 days) and dexamethasone.

### Experimental group

The acupoints are located according to the *WHO standard acupuncture point locations in the Western Pacific Region* [13]. Zusanli (ST36): below the knee, 3 *cun* below Dubi (ST35) on the line between Dubi (ST35) and Jiexi (ST41). Zhongwan (CV12): on the anterior midline of the abdomen, 4 cun above the umbilicus.

The needles (0.3 cun; Hua Tuo, Jiangsu, China) will be inserted and manipulated until De Qi (a sensation of soreness and tingling) is reported by the patient. Then the needle is connected to a Hua Tuo electroacupuncture therapy apparatus. Another refined electrode side will then be attached 1 cm beyond the acupoint. The frequency used is as in Shen et al. [14]; a bilateral 2-Hz current under 10 mA. The needles are left in place for 30 minutes. The treatment is delivered 30–60 minutes prior to commencement of chemotherapy. The therapy is delivered for 4 consecutive days.

### Outcomes

#### Primary outcome

The evaluation of nausea and vomiting is classified by the incidence of nausea and vomiting. In this trial, we use the Rhodes Index of Nausea, Vomiting and Retching [15] to score the incidence of nausea and vomiting. It could also be used to evaluate the duration, frequency, and severity of nausea and vomiting.

#### Secondary outcome

The Functional Assessment of Cancer Treatment (FACT) will be used to explore physical well-being (PWB), social well-being (SWB), emotional well-being (EWB), and functional well-being (FWB). The Hospital Anxiety and Depression Scale (HADS) will be used to identify anxiety and depression levels in the patients.

### Safety

Routine blood tests, liver/kidney function, constipation, diarrhea, and other antiemetic side effects, or adverse reactions will be assessed.

### Randomization and allocation concealment

This trial is randomized by a central randomization system. Eligible participants are randomly assigned to each group at a ratio of 1:1:1:1. Only the operational assistants log into http://www.tcmcec.net:8082/wcr/login.aspx and fill in the basic information of the subjects to apply a random number and distribution of constituencies. Stochastic systems are served by an independent third party, the Clinical Evaluation Center, China Academy of Traditional Chinese Medicine.

### Blinding

The participants, operational assistants, evaluators, and statisticians will be blinded to the treatment allocations, which will not be revealed until the end of the study. We have described for each included study the methods used to blind study participants and personnel from knowledge of which intervention a participant received. To prevent performance bias, studies are judged at low risk of bias if they were blinded or if we judged that the lack of blinding could not have affected the results. Evaluators and operational assistants will not work together at the same time. There will be no communication between patients. The evaluators will not be able to ask whether the patients receive the acupuncture or not or where the acupoints are. There will be no opportunities for the statisticians to become aware of the constituency distributions.

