## Discussion

The mechanism of CINV is complicated. What we know at present is that the 5-HT system and SP system may have an important role in CINV. 5-HT is mainly involved in the process of acute nausea and vomiting [15]. During chemotherapy, enterochromaffin cells (EC) release 5-HT receptors and vagal afferent nerves have been shown to be activated by 5-HT receptors. The signal is passed by the dorsal motor nucleus of the vagal nerve (vomiting center), which causes severe vomiting [16]. The SP system participates in the process, which prolongs the nausea and vomiting [17]. During long-term chemotherapy, cell apoptosis and inflammation induce EC to release P substances combined with NK-1 on the chemoreceptor trigger zone by the vagal afferent nerves. Then the signal reaches the stomach through the vagal efferent fibers, which delays nausea and vomiting [18]. It has been shown that the dopamine system plays an important role as well in the occurrence of CINV, but the specific mechanism is unclear [19].

Electroacupuncture, in particular, has been shown to inhibit SP and 5-HT release in EC. It may directly inhibit afferent vagal nerve excitability, or it may inhibit the solitary tract nucleus or vagal nerve dorsal nucleus as the acupuncture signals are conducted through the sensory nerves through the spinal cord upwards to the central level. Thus, CINV could be reduced. However, the choice of acupoints may also alter the efficacy of EA treatment. Clinical studies are still unable to provide guidance for the prevention of or treatment for CINV. Further, there is a lack of sufficient clinical evidence as to how acupoint-matching may improve CINV [20].

In terms of the risk of bias, derived from the partial absence of blinding of the interventionists, it is difficult to implement a fully blind method for the operators because acupuncture is a physical operation method, and the interventionists are required to be knowledgeable about acupuncture.

Nevertheless, the results of this trial are expected to explore the effects of the matching of different acupoints and offer biologic plausibility for the use of acupuncture in the treatment of CINV.

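### The protocol says participants are blinded, but an antiemetic-only control without sham makes this impossible, so comparisons with control on patient-reported outcomes include expectation and attention

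*Protocol article*

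**What the plan says.** All references are to the protocol article.

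- **Blinding:** "The participants, operational assistants, evaluators, and statisticians will be blinded to the treatment allocations". This is to hold until the trial ends. The section adds that evaluators and operational assistants do not work together, that patients do not communicate with one another, that evaluators may not ask about needling or its site, and that statisticians cannot learn the groups.
- **Control group:** "The control group will receive only a basic antiemetic regimen". No sham procedure is described.
- **Interventions:** "The remaining three groups will be given antiemetics and receive electroacupuncture at the ST36, CV12, and ST36-CV12 points".
- **Experimental group:** the needles "will be inserted and manipulated until De Qi (a sensation of soreness and tingling) is reported by the patient" and are then connected to a stimulator for 30 minutes on 4 consecutive days. One point is on the leg ("Zusanli (ST36): below the knee"); the other, CV12, is on the abdomen.
- **Randomization and allocation concealment:** "Only the operational assistants log into" the central system, where they enter the participant's details and apply for the random number and group.
- **Discussion:** the risk of bias is described as "derived from the partial absence of blinding of the interventionists". Participants are not mentioned.

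**The concern.** A trial in which one arm has no needling and no sham cannot hide from patients whether they received electroacupuncture. The Blinding section says that it does, and the Discussion limits the admitted gap to the people delivering treatment.

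This matters because of what is measured. The Rhodes index (the primary outcome) and the nausea VAS record what the patient experiences; so, by inference from what they measure, do FACT and HADS. A difference between a needled arm and control on these outcomes can come from the stimulation, from expecting benefit, or from the extra attention over four daily sessions. A reader who relies on the Blinding section would rule out the last two and rate the trial as participant-blinded. The sample size itself rests on one such comparison, CV12 against control.

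**Working it through.** **1. Participant blinding, section against section.**

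| Question | Blinding section | Treatment sections |
|---|---|---|
| Can a patient tell electroacupuncture from control? | No, by the claim | Yes: needles, a sensation the patient must report, and current, against antiemetics alone |
| Can a patient tell the needled arms apart by site? | No, by the claim | Yes: leg, abdomen or both |

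The ban on evaluators asking about needling or its site is useful only if patients know the answer. The ban on contact between patients can keep them from comparing treatments, but it does not hide from a patient what was done to him or her.

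**2. Operational assistants.** The Blinding section calls them blinded. The randomization section makes them the only people who apply for the assignment. The Discussion says that full blinding of operators is difficult. These three statements do not fit together.

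**3. Sentences that describe no procedure of this trial.** The Blinding section speaks of methods described for each included study and of studies being judged at low risk of bias. This is systematic-review wording and gives no support to the claim.

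**4. The plan's own figure, for background.** Inputs from the Sample size calculation section: means 1.18 and 1.82 (difference 0.64), SDs 0.53 and 0.69, two-sided alpha 0.05/6 = 0.0083, power 90%.

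- Pooled SD = √[(0.53² + 0.69²)/2] = 0.615.
- n per arm = 2 × 0.615² × (2.638 + 1.282)² / 0.64² = 28.4, so 29 by the normal approximation and 31 by the exact t calculation. The protocol states 27, which is close.

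The blinding point does not depend on this figure.

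**5. Illustration of size.** Assumption: there is no specific effect, and expectation alone shifts the score by d standard deviations. The documents give no value for d, so a range is shown. With 40 per arm, the noncentrality is d × √(40/2) = 4.472 d, and the two-sided critical t at 0.0083 on 78 degrees of freedom is 2.707.

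| Assumed shift d | Noncentrality | Probability of p < 0.0083 |
|---|---|---|
| 0 | 0 | 0.8% |
| 0.2 | 0.894 | 3.9% |
| 0.3 | 1.342 | 9.2% |
| 0.4 | 1.789 | 18.7% |
| 0.5 | 2.236 | 32.6% |

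On the pilot vomiting-experience score, 0.2 to 0.5 SD is 0.12 to 0.31 points. This conversion applies to that score only, because no SD is given for the VAS, FACT or HADS.

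**The case against.** The strongest reply is that the protocol does contain real safeguards. Evaluators work apart from the operational assistants and may not ask about needling, statisticians are kept from the groups, and the data storage section separates operator, evaluator and statistician. A reader might infer from the false participant claim that the trial has no protection against performance or detection bias, or is open-label throughout. The documents do not support that. Evaluator and statistician masking can stand as described; what fails is masking of participants and, probably, of the assistants.

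Four further objections have weight.

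- **The assistants.** The randomization section is unclear about what the system returns and who reads it. That the assistants see the group is a likely inference, not a stated fact, and the Discussion already concedes part of this if they are the same people as the operators. The point is therefore secondary.
- **Self-report.** The article does not say who completes the scales. For FACT and HADS, patient report is inferred from what they measure. If an evaluator fills in the form, the content still comes from an unblinded patient.
- **Size.** The calculation rests on an assumed shift. It would also be wrong to extend it to all needled patients pooled against control on a continuous score: the Statistical analysis section plans a four-group test with pair-wise comparisons, and contrasts electroacupuncture with antiemetics alone only for complete response in subgroups.
- **Harder outcomes.** Vomiting frequency and use of remedy drugs are already to be collected, so asking for them adds nothing. Remedy drugs are prescribed by a doctor whose masking is not described, so that outcome is not clearly protected either.

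An add-on comparison without sham is a legitimate design. The objection to the statement about blinding is not an objection to the design.

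**Conclusion.** The statement that participants are blinded is wrong as written, and nothing in the article reconciles it with the treatment sections. Participants cannot be blinded to electroacupuncture versus control or to needle site. The conflict over the operational assistants is real but less certain.

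Of the six pair-wise comparisons among four arms, the three against control are fully exposed. The three among needled arms are less exposed, since every patient there is needled, but they are not site-blind, and the matching arm receives an extra point.

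The size cannot be established from the documents. Under the assumed shift of 0.2 to 0.5 SD, with 40 per arm and two-sided alpha 0.0083, a null comparison with control would be declared significant with probability about 4% to 33% rather than 0.8%. The contradiction stands whatever the shift.

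**What to change.** - Restate the Blinding section: participants, and those who deliver the treatment or obtain the assignment, are not blinded; evaluators and statisticians are. Bring the randomization section and the Discussion into line with this.
- Delete the sentences about included studies and their risk of bias.
- State that electroacupuncture-versus-control contrasts estimate the whole treatment package, including expectation and attention, and will not be read as point-specific efficacy.
- Draw point-specific conclusions from contrasts among the three needled arms, noting that patients there still know the site and number of points.

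The cost is wording and a narrower conclusion. The sample size, planned tests, staff and procedures do not change, so the correction can be made while the trial is recruiting.

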### Participant timeline

The enrollment will be carried out before the first day of chemotherapy on day 0. The electroacupuncture intervention will be given once daily from day 1 to day 4. All assessments will be scheduled from day 0 to day 5 (Fig. 1)

### Quality control

#### Clinical quality control

Level 1 examination (quality control) is conducted by the quality inspectors. They are required to develop quality checklists for all research data sources, data reporting, and adverse events. During the quality control process, they will need to take appropriate measures to assess quality problems and sign on the checklist. In Level 2 examinations (inspection), audit procedures and project sheets are in accordance with the progress of the completion of the test, the subjects in the group, and the relevant inspection project. The inspectors need to complete audit reports during the treatment. For the Level 3 examination (audit), case report form (CRF) management and assessment of the authenticity of the case will be carried out by the Clinical Evaluation Center, China Academy of Traditional Chinese Medicine.

### Document management and standardization of clinical treatment

To standardize clinical operations and deliver clinical quality assurance, we developed a series of documents and standardized clinical management operating specifications. Developing appropriate standard operating norms for various stages of clinical research is a way to ensure homogeneity between various researchers. It is helpful to use file management and develop a standard operating procedure (SOP) to ensure the feasibility, safety, and scientific integrity of clinical research.

### Data storage and confidentiality

The Clinical Evaluation Center, China Academy of Traditional Chinese Medicine provides a central stochastic system, database development, data entry and cleaning, data verification, statistical analysis, and other services as an independent third party. To reduce the risk of selection bias, the operator, evaluator, and statistician are separated.

### Statistical analysis

Statistical analysis will be conducted using SPSS (v.22; IBM Corp, Armonk, NY, USA). We will express normally distributed continuous outcomes using mean (SD) and skewed data with median (range). Dichotomous outcomes will be expressed as frequency or incidence. If the data are normally distributed, we will use ANOVA with Bonferroni-corrected pair-wise comparisons to compare the primary outcomes among the four treatment groups. If the data are not normally distributed, we will use a Kruskal-Wallis test to compare the four treatment groups and a Wilcoxon rank-sum test for the pair-wise comparison for the primary outcome. Intergroup differences in categorical data (Common Terminology Criteria for Adverse Events) will be assessed using the chi^2^ test or Fisher exact tests (two-tailed), as appropriate. Repeated measures analysis of variance (R-ANOVA) will be used to assess the frequency of vomiting, and the Visual Analogue Scale for nausea and nausea and vomiting and retching among the four study groups. Length of no days of nausea and vomiting will be calculated using Kaplan-Meier analysis and compared among the groups using the log-rank test. Subgroup analysis based on single or multiple chemotherapy sessions will be performed to compare the efficacy of basic antiemetic regimens plus electroacupuncture or an antiemetic regimen only on inducing a complete response. A *p* value <0.05 will be considered to be statistically significant.

## Discussion

The mechanism of CINV is complicated. What we know at present is that the 5-HT system and SP system may have an important role in CINV. 5-HT is mainly involved in the process of acute nausea and vomiting [15]. During chemotherapy, enterochromaffin cells (EC) release 5-HT receptors and vagal afferent nerves have been shown to be activated by 5-HT receptors. The signal is passed by the dorsal motor nucleus of the vagal nerve (vomiting center), which causes severe vomiting [16]. The SP system participates in the process, which prolongs the nausea and vomiting [17]. During long-term chemotherapy, cell apoptosis and inflammation induce EC to release P substances combined with NK-1 on the chemoreceptor trigger zone by the vagal afferent nerves. Then the signal reaches the stomach through the vagal efferent fibers, which delays nausea and vomiting [18]. It has been shown that the dopamine system plays an important role as well in the occurrence of CINV, but the specific mechanism is unclear [19].

Electroacupuncture, in particular, has been shown to inhibit SP and 5-HT release in EC. It may directly inhibit afferent vagal nerve excitability, or it may inhibit the solitary tract nucleus or vagal nerve dorsal nucleus as the acupuncture signals are conducted through the sensory nerves through the spinal cord upwards to the central level. Thus, CINV could be reduced. However, the choice of acupoints may also alter the efficacy of EA treatment. Clinical studies are still unable to provide guidance for the prevention of or treatment for CINV. Further, there is a lack of sufficient clinical evidence as to how acupoint-matching may improve CINV [20].

In terms of the risk of bias, derived from the partial absence of blinding of the interventionists, it is difficult to implement a fully blind method for the operators because acupuncture is a physical operation method, and the interventionists are required to be knowledgeable about acupuncture.

Nevertheless, the results of this trial are expected to explore the effects of the matching of different acupoints and offer biologic plausibility for the use of acupuncture in the treatment of CINV.

### Trial status

The trial is currently recruiting patients.

## Abbreviations

ALT: Glutamic-pyruvic transaminase
AST: Glutamic oxaloacetic transaminase
BUN: Blood urea nitrogen
CINV: Chemotherapy-induced nausea and vomiting
Cr: Urine creatinine
CRF: Case report form
CV12: The Zhongwan acupoint
FACT-G: Functional Assessment of Cancer Therapy - General
KPS: Karnofsky score
NIH: National Institutes of Health
ST36: The Zusanli acupoint
TBIL: Total bilirubin
